
### Qualitative data

To explore perceived barriers and facilitators to the intervention, as well as acceptability and satisfaction with participation, individual semi-structured interviews will be conducted [37]. The interviews will take place after 4 months and will be held at the most convenient location for the participants (home, hospital outpatient clinic or via telematics). To facilitate the participants’ response a track guide will be followed (Table 3).

**Table 3 tbl0003:** Interview guide.

Questions
Q1) Please could you tell me what prompted you to participate in the study?
Q2) Thinking back to the meeting you had with the nurse before discharge, do you remember what you talked about? How did you feel during that meeting? In your opinion, was it helpful/important?
Q3) Once at home, did you have difficulty using the system for measuring vital signs? Did you need someone to help you?
Q4) Regarding self-monitoring, were you able to measure your vitals every day as required?
Q5) Compared to your telephone support intervention up to now, how do you rate the quality of the support you receive? Do you feel that the way of communication used has influenced the accuracy of the information provided?
Q6) Can you remember situations in which you feel you did not receive adequate support? Can you tell me about that incident? In your opinion, what could have been done differently? Why?
Q6) Overall, do you feel satisfied with the care you received? If you had the opportunity, what would you change about the suggested intervention? Why?

Each participant will sign an independent informed consent before beginning the interview. Confidentiality will be guaranteed by using identification numbers. The interview can be interrupted by the patient at any time.

### Statistical methods

Data will be stored using REDCap (Research Electronic Data Capture), a secure web-based application developed to support data capture [38]. For quantitative data, a descriptive analysis will be conducted, considering the nature of the variables. If feasible, comparisons of characteristics and outcomes between the intervention and control groups will be made using parametric or non-parametric tests, depending on the distribution of the variables.

For qualitative data, a qualitative descriptive approach will be used [39]. Interviews will be audio-recorded and transcribed *verbatim* within 48 h. Data will be analyzed according to content analysis method [40], which comprises the following steps. 1) Familiarization: the interviews will be carefully and repeatedly read; 2) Compilation: two independent researchers will review each interview, identifying the most significant words and phrases (units of meaning); 3) Condensation: a descriptive label (code) will be attributed to each meaning unit; 4) Categories: similar codes will be grouped into categories; 5) Themes: similar categories will be condensed into themes.

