**Table utbl0001:** 

Subject area:	Medicine and Dentistry
More specific subject area:	*Geriatric care*
Name of your protocol:	INTERCOACH
Reagents/tools:	*Mini-COG* *Edmonton Symptom Assessment System (ESAS)* *Cumulative Illness Rating Scale (CIRS)* *European Health Literacy Survey* *SF-12 Questionnaire* *Self-Care Of Heart Failure (SCHF v. 7.2)* *Heart Failure Somatic Perception Scale v.3 (HFSPS)* *Self-Efficacy Scale* *Geriatric Depression Scale short version* *Hamilton Anxiety Scale*
Experimental design:	*A prospective, open label randomized controlled feasibility study will be conducted, with a 1:2 ratio between intervention and control groups. Participants assigned to the intervention group will receive the following educational program in addition to standard care: 1) an in-person educational intervention before discharge, following the recommendations of the European Society of Cardiology; 2) a nurse-led telephone coaching service (once a week for the initial month, followed by sessions every two weeks); 3) a daily home-based self-telemonitoring system for weight, blood pressure, heart rate, and oxygen saturation. Vital signs will be transmitted to a platform and remotely monitored by a nurse. A structured intervention protocol will be activated based on the patient's clinical conditions.*
Trial registration:	*The study protocol has been registered in the Clinicaltrials.gov:**NCT06285565*
Ethics:	*The study protocol was submitted and approved by the Ethics Committee of Maggiore della Carità Hospital of Novara in December 2023 (*CE390/2023). *The study will adhere to the Ethical Principles of the Declaration of Helsinki, as well as the European Union Standards of Good Clinical Practice* *The data from the feasibility study will be combined with those from the definitive study if it validates the suggested intervention and no substantial corrections will be required.*
Value of the Protocol:	(1) *This protocol is important to inform the design of a definitive RCT, aimed to assess the effectiveness of a remote nurse-led coaching intervention with a home telemonitoring program.* (2) *Given the complexity of the supportive intervention, it is crucial to involve patients in the research process and to collect their preferences regarding the intervention.* (3) *3) This feasibility study is important to define a successful care plan that guarantees follow-up for patients with heart failure*.

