### Aim of the study

The primary aim of the study is to investigate the feasibility and acceptability of a home telemonitoring program combined with telephone-delivered nurse-led coaching intervention.

The secondary aim is to explore the feasibility of a randomized controlled study to assess the effectiveness of the supportive intervention.

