### Outcomes measured

Four aspects of feasibility will be the focus of the outcomes’ measurement [22]:-Process: evaluates the feasibility of the study's fundamental steps (e.g. recruitment rate).-Resource: investigates potential time and resource problems during the study (e.g. retention rate, adherence to the coaching intervention, adherence to the telemonitoring program, and the amount of time spent by nurses each week on coaching interventions).-Management: examines possible issues related to patient and data handling (e.g. frequency of calls made by patients to the nurse, the acceptability of the intervention to patients, completeness of data collection).-Scientific value: describes how treatment safety, response, effect, and effect variance are evaluated (patient's self-care capacity, self-efficacy, quality of life, somatic perception of the disease, emotional and psychological well-being, mortality, all-cause hospital admissions, HF-related hospital admissions, etc.)

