The following outcomes will be measured:-*Recruitment rate:* the proportion of patients who agreed to participate relative to those who fulfilled the inclusion criteria.-*Retention rate*: the proportion of patients who complete the study relative to those who consent to participate.--*Adherence to the coaching intervention:* the number of coaching phone calls scheduled relative to those actualized.-*Adherence to telemonitoring program:* the proportion of days during which vital signs were measured and sent by the system relative to the total duration of the intervention.-*Weekly time dedicated to coaching intervention by the nurse* (in hours).-*Completeness of data collection:* the number of returned questionnaires.-*Number of weekly calls made by patients to the nurse.*-*Quality of life*: Quality of life is a value that integrates objective (physical health, personal circumstances, social relationships, social and economic influences) and subjective indicators (such as how the individual responds to objective conditions), related to various dimensions of life and personal values [28]. This outcome will be assessed using the Italian version of the SF-12 scale [29]. This is a multidimensional scale consisting of 12 questions related to physical functioning, limitations due to physical health or emotional factors, energy and fatigue, emotional well-being, social activities, pain, and general health perception. The scale collects self-report data using a Likert scale. The score for each subscale will be standardized on a 0–100 scale, where higher values indicate better quality of life.-*Self-care capacity*: The self-care capacity of the patient encompasses three dimensions: self-care maintenance, symptom perception, and self-care management [30]. Self-care maintenance reflects the active commitment and responsibility for one's own care, as well as the behaviors adopted to maintain physical and emotional stability (e.g., adherence to therapy). On the other hand, symptom perception refers to the ability to respond to signs and symptoms of disease exacerbation when they occur, such as by searching for help (self-care management) [30]. The self-care capacity will be evaluated using the Italian version of the Self-Care of Heart Failure Index (SCHF v. 7.2) [31]. The tool consists of three different scales: self-care maintenance (10 items), symptom perception (11 items), and self-care management (8 items) producing a standardized score of 0–100, where higher values refer to the greater self-care capacity. A score ≥70 indicates adequate self-care capacity.-*Self-Efficacy Scale:* Self-efficacy perception refers to the individual's belief in their ability to achieve certain goals because of their actions, regardless of the challenges and difficulties they may face [32]. Self-efficacy is a mediator of self-care capacity [32]. A scale consisting of 10 items using a 5-response Likert scale will be utilized [33].-*Heart Failure Somatic Perception Scale v.3* (HFSPS) [34]. HF is a complex clinical syndrome characterized by several signs and symptoms, including shortness of breath, fatigue, and peripheral fluid accumulation [23]. To measure this outcome, we will employ a scale comprising four factors, which evaluate the presence and impact of 18 typical signs and symptoms of HF experienced by the patient in the preceding week. Each item has 6 response options ranging from 0 (I do not have this symptom) to 5 (extremely severe), with a range from 0 to 90, where high scores lead back to a greater impact of symptoms on the patient.-*Geriatric Depression Scale short version* (GDS) [35] for detecting depressive symptoms of the elderly. It consists of 15 questions involving a dichotomous response (yes/no). Ten questions are indicative of depression for positive responses, while the remaining five (items 1, 5, 7, 11, 13) for negative responses. Scores 0–4 are considered normal, depending on age and education; scores between 3 ± 2 are associated with the absence of depressive symptoms, 7 ± 3 mild depression, and 12 ± 2 depression.-*Hamilton Anxiety Scale* [36]: for the assessment of anxiety symptoms (psychological and somatic). The scale consists of 14 items, rated on a 4-point Likert scale (0=not present; 4= severe), with a range of total score from 0 to 56, where values ≤ 17 indicate mild anxiety, 18–24 moderate anxiety and ≥ 25 severe anxiety.-*Hospital readmissions at 90- and 180- days* after hospitalization for all causes and HF-related, Emergency Departments visits, outpatient visits, General Practitioner visits, and mortality.

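### The plan's only named method for comparing outcomes between 15 and 30 patients is significance testing, if feasible, where its stated purpose calls for estimated differences with 95% intervals

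*Protocol article*

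**What the plan says.** The Protocol article's *Statistical methods* sets the base analysis first: "For quantitative data, a descriptive analysis will be conducted, considering the nature of the variables". It then adds that, if feasible, "comparisons of characteristics and outcomes between the intervention and control groups will be made using parametric or non-parametric tests". The choice of test family is left to the distribution of each variable. Testing is the only method named for comparing the arms.

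*Aim of the study* puts feasibility first: "The primary aim of the study is to investigate the feasibility and acceptability of a home telemonitoring program". *Sample size* gives 45 patients, 15 intervention and 30 control, and says that no calculation is required for a feasibility study.

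The clinical and patient-reported outcomes form the last of four feasibility domains in *Outcomes measured*. That domain "describes how treatment safety, response, effect, and effect variance are evaluated". *Quantitative data* lists the questionnaires and then readmissions at 90 and 180 days "after hospitalization for all causes and HF-related, Emergency Departments visits, outpatient visits, General Practitioner visits, and mortality". Table 2 marks these outcomes at both T1 (3 months) and T3 (6 months). No outcome or time point is named as the main one. The specifications table gives the purpose: "This protocol is important to inform the design of a definitive RCT, aimed to assess the effectiveness".

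**The concern.** The method named does not match the product wanted. A definitive trial is planned from the size of a difference, its uncertainty and the outcome's variability. A p-value gives none of these, and with 15 against 30 patients it says little in either direction. A non-significant result is compatible with a worthwhile effect. A significant one, picked out of many unranked comparisons, may well be chance.

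The words 'if feasible' govern whether the tests are run. They do not say how the results would be read. If the tests are run across the whole list, the report is quite likely to contain one or more p-values below 0.05 even if the programme does nothing, and the article says nothing to stop a reader taking these as signs of benefit.

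**Working it through.** The plan states no alpha, power or error rate, so it has no figure of its own to reproduce. The arm sizes agree with the 1:2 ratio: 15 + 30 = 45.

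**Step 1. Count the outcomes.** Table 2 has 12 clinical and patient-reported rows marked at both T1 and T3: HF-related readmission, all-cause readmission, outpatient visits, GP visits, emergency visits, quality of life, self-care, self-efficacy, somatic perception, anxiety, depression and mortality. *Quantitative data* describes self-care as three scales, so the count becomes 12 + 2 = 14. Reporting the SF-12 as two scores, which is an assumption, gives 15. Two time points give 24 to 30 possible tests.

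**Step 2. Independent tests.** Assume two-sided 0.05 per test and no true effect. The chance of at least one p<0.05 in k tests is 1 − 0.95^k:

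| k | 12 | 14 | 15 | 24 | 28 | 30 |
|---|---|---|---|---|---|---|
| Chance | 0.460 | 0.512 | 0.537 | 0.708 | 0.762 | 0.785 |

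Whatever the correlation, the expected number of false positives in 30 tests is 30 × 0.05 = 1.5.

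**Step 3. Correlated tests, by simulation, 15 vs 30, no effect.** Three set-ups were used:

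- A: 30 normal outcomes with one common correlation, t-tests, 10,000 replicates.
- B: 15 normal outcomes at 2 time points, t-tests, with the same outcome correlated 0.5 to 0.7 over time.
- C: as B with time correlation 0.6, but with 9 continuous scores (t-test), 3 binary outcomes (Fisher) and 3 counts (Mann-Whitney), at assumed event rates.

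| Correlation between outcomes | A | B | C |
|---|---|---|---|
| 0 | 0.785 | 0.73–0.77 | 0.72 |
| 0.3 | 0.674 | 0.65–0.68 | 0.63 |
| 0.5 | 0.513 | 0.54–0.58 | 0.54 |
| 0.7 | not run | 0.39–0.42 | 0.42 |
| 0.8 | 0.259 | not run | not run |

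A separate run of set-up A gave 0.80, 0.66, 0.52 and 0.27 at correlations 0, 0.3, 0.5 and 0.8. With only the 12 table rows at two time points, set-up B gives 0.64–0.68, 0.58–0.61, 0.49–0.52 and 0.37–0.39 at correlations 0, 0.3, 0.5 and 0.7. With 15 tests at a single time point, set-up A gives 0.54, 0.46, 0.37 and 0.21 at 0, 0.3, 0.5 and 0.8.

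**Step 4. What one comparison can show.** For a continuous score, the standard error of the difference in SD units is √(1/15 + 1/30) = √0.1 = 0.316. The 95% half-width is 2.017 × 0.316 = 0.64 SD (t quantile on 43 degrees of freedom). A true difference of 0.5 SD would reach p<0.05 with probability Φ(0.5/0.316 − 1.96) = Φ(−0.38) = 0.35. A difference of about 0.91 SD would be needed for 80% power. An interval shows this imprecision, and a p-value hides it.

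**Step 5. The largest difference.** With no effect, the largest of 30 absolute standardised differences in set-up A averages 0.67 SD at correlation 0.5 (0.76 at 0, 0.54 at 0.8). A difference picked because it stands out would therefore be a poor planning value.

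**The case against.** The strongest reply is that this is a feasibility study and says so throughout. Its base analysis is descriptive, the tests are conditional, no alpha or efficacy hypothesis is stated, and no significance claim is announced. Test ordering and multiplicity rules commonly sit in a full protocol or analysis plan that is not shown. The descriptive analysis may also report means and SDs by arm, which would cover part of the need for effect variance.

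Most of this stands, and it rules out several stronger readings that a reader might infer:

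- *That the outcomes will certainly be tested and a useless programme will look effective about half the time.* The tests are conditional, and 'about half' is one point in a wide range that rests on an assumed alpha and an assumed correlation.
- *That the missing hierarchy or multiplicity rule is itself a defect.* It may be in an analysis plan that is not shown.
- *That the best-looking outcome will become the definitive trial's primary outcome, or its observed effect the planning value.* No section says so. Choosing outcomes is a legitimate product of a feasibility study.
- *That a chance p-value would trigger pooling with the definitive trial.* The specifications table makes pooling depend on the study validating the intervention, but does not tie that to any test.

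The reply does not remove the mismatch. *Statistical methods* names a method for comparing outcomes between arms, and it is testing. Reporting by arm does not give the between-arm difference with its uncertainty.

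**Conclusion.** The point holds in a limited form. The article provides, conditionally, for significance tests of 12 to 15 unranked outcomes at two time points in 15 against 30 patients, while its stated need is effect and effect variance for a definitive RCT. Estimates with intervals serve that need and tests do not.

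If 30 tests were run with no true effect, the chance of at least one nominal p<0.05 would be roughly 25% to 80%, and about 50% at a correlation of 0.5. This rests on two-sided 0.05 (assumed), two SF-12 scores (assumed) and an unknown correlation. The mixed continuous, binary and count set-up gives a similar picture, 42% to 72% over correlations 0.7 to 0. This is an improvement the sponsor should make. It is not evidence that the trial makes an unsound confirmatory claim.

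**What to change.** In *Statistical methods*, replace the tests of outcomes with estimated between-arm differences (or ratios, for visits and events) with 95% confidence intervals. State that these comparisons are exploratory and that no p-value will be used to judge the intervention. Possible wording: *Between-arm comparisons of outcomes are exploratory. Each will be reported as an estimated difference or ratio with a 95% confidence interval, and no p-value will be used to judge the intervention.*

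The cost is two sentences, with no new data and no change to the sample or schedule. The downside is that the report can no longer present an isolated p<0.05 as evidence of benefit. Naming in advance a candidate primary outcome for the definitive RCT is optional and not part of this fix.

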## Methods

### Study design and randomization

A parallel, open label randomized controlled feasibility study will be carried out utilizing a mixed method approach. The protocol complies with the criteria reported by SPIRIT 2013 statement [20]. We will generate a list of randomizations stratified by wards and gender, with a 1:2 ratio between intervention and control groups, using web-based software.

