### Sample size

As this is a feasibility study, it is not required to calculate the sample size [22]. Instead, the sample must be representative of the reference population [22]. Accordingly, it is planned to recruit 45 patients (15 will be allocated to the intervention arm and 30 to the control arm).

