### Control group

Participants who will be randomized to the control group will receive the usual care, which follows clinical guidelines [23].

For patients admitted to one out of three wards, an outpatient visit will be scheduled one month after discharge. However, no follow-up will be planned for patients discharged from the other two wards.

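### The only between-arm method stated is a two-group test picked by distribution; it names neither the baseline scores nor the randomisation strata and commits to no effect estimate with an interval

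*Protocol article*

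**What the plan says.** Under Statistical methods, the protocol article first states that "a descriptive analysis will be conducted, considering the nature of the variables". It then adds that, where feasible, the arms will be compared on both characteristics and outcomes "using parametric or non-parametric tests, depending on the distribution of the variables". It gives no other between-arm method for the quantitative data.

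Four other places bear on this:

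- **Study design and randomization:** the list is "stratified by wards and gender, with a 1:2 ratio between intervention and control groups".
- **Control group:** one ward schedules an outpatient visit at one month, whereas "no follow-up will be planned for patients discharged from the other two wards".
- **Table 2:** quality of life, self-care, self-efficacy, somatic perception, anxiety and depression are measured at T0, 3 months and 6 months. Readmissions, visits and mortality are recorded at 3 and 6 months only.
- **Outcomes measured:** the scientific value domain "describes how treatment safety, response, effect, and effect variance are evaluated".

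**The concern.** The study's product for a later trial is a set of planning values. The Abstract says it should inform a definitive RCT, and the Protocol validation section says that no preliminary data exist. For that purpose one needs, for each scale, a between-arm difference with its interval, the SD that will apply in the later analysis, and the correlation between baseline and follow-up. A test whose form depends on the distribution settles on no single effect measure, and a rank test by itself reports no mean difference.

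The stated comparison also makes no mention of two pieces of design information that are already available. T0 scores usually carry information on later scores. Ward may too, because usual care differs by ward.

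The same sentence covers baseline characteristics. After randomisation, a significance test of those asks only whether chance produced the differences, which is already known if allocation worked.

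At stake are wider intervals than the data require, and a small-sample p-value that is easily misread as evidence of no effect.

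**Working it through.** **Inputs from the protocol article.** 45 patients, 15 intervention and 30 control (Sample size); three wards and two genders, hence six strata (Population and enrollment; Study design and randomization). The split agrees with the 1:2 ratio: 45 × 1/3 = 15 and 45 × 2/3 = 30. The article gives no alpha, power, effect size or SD, so it has no precision figure to reproduce.

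**Assumptions, not in the documents.** Two-sided 5% level; correlation ρ between T0 and follow-up of 0.3 to 0.7; strata that explain nothing beyond T0; an illustrative effect of 0.5 SD.

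**Unadjusted comparison, in SD units.**

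- SE = √(1/15 + 1/30) = √0.100 = 0.316
- 95% half-width = t(43 df) × SE = 2.017 × 0.316 = 0.638
- Difference detectable with 80% power: 0.91 SD. Power at 0.5 SD: 0.34.

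**Linear model with arm, T0, ward (two terms) and gender (one term).**

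- Residual df = 45 − 6 = 39
- SE = 0.316 × √(1 − ρ²) × √(1 + 1/41), where the last factor allows for chance T0 imbalance
- By the variance factor alone, 45 patients are worth 45/(1 − ρ²) unadjusted patients

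| ρ | 95% half-width (SD) | Change from 0.638 | 45/(1 − ρ²) | Power at 0.5 SD |
|---|---|---|---|---|
| 0 | 0.647 | 1.5% wider | 45 | 0.33 |
| 0.3 | 0.618 | 3% narrower | 49 | 0.36 |
| 0.5 | 0.561 | 12% narrower | 60 | 0.42 |
| 0.7 | 0.462 | 28% narrower | 88 | 0.57 |

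If 20% were lost to follow-up (assumed; 12 v 24), the unadjusted half-width would be 0.72 SD, and the adjusted values 0.70, 0.635 and 0.52 SD at ρ = 0.3, 0.5 and 0.7.

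**Cost of the ward and gender terms.** At ρ = 0.5 the half-width is 0.559 SD with T0 alone and 0.561 SD with T0, ward and gender. Three extra terms therefore cost under 0.5% when the strata are not prognostic. Main effects are preferable to six cells, which would average 45/6 = 7.5 patients, of whom 15/6 = 2.5 are in the intervention arm.

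**Does picking the test do harm in itself?** This was simulated with 15 v 30, 2,500 runs per setting, a Shapiro-Wilk test choosing between the t-test and Mann-Whitney, and the linear model adjusted for T0 only.

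- Type I error of the picked test: 0.044 to 0.054. There is no material inflation.
- Normal data, effect 0.5 SD: power 0.33 to 0.35 for the picked test, and 0.35 to 0.56 for the adjusted model over ρ = 0.3 to 0.7.
- Strongly skewed (log-normal) data, same effect: about 0.73 to 0.75 for the picked test, and 0.43 to 0.59 for the adjusted model on raw scores.

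**What the descriptive analysis already gives.** Arm means and SDs yield an unadjusted difference. The pooled SD on 43 df has 95% limits of 0.83 to 1.27 times its estimate.

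**The case against.** The article is a condensed account, and its full protocol and analysis plan are not shown. Covariates and intervals are often left to those documents. The comparison is conditional on feasibility and secondary to a descriptive analysis, in a study whose aims are feasibility and acceptability and whose size was not derived from power. The correlation is assumed, and a non-parametric option is defensible for bounded or skewed scales.

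Most of this stands, and it rules out three stronger readings.

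- A reader might infer that the analysis will ignore T0 and the strata. The text only fails to name them; no sentence excludes them.
- A reader might infer that the study will not yield an effect or its variance. The descriptive analysis allows both, unadjusted. What is absent is a commitment to an estimate with an interval, and to the residual SD and correlation that an adjusted definitive trial would be planned on.
- A reader might infer that choosing the test by distribution inflates false positives. The simulation does not show this, and under strong skew the rank test had more power than the adjusted model on raw scores. Nor does the article say outright that the choice follows inspection of the trial data.

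The objection does not remove the point, because the article does state a method, and an analysis plan that followed it would inherit its weakness. That the study was not sized for a hypothesis test is itself a reason to report an estimate rather than rely on a test.

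**Conclusion.** The point holds as a worthwhile, inexpensive improvement to a conditional, secondary analysis. It does not threaten the study's feasibility conclusions.

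For the T0-measured scales the gain in precision is substantial at correlations of 0.5 to 0.7 and slight at 0.3. These figures rest on the assumed correlations, full follow-up of 45 patients and strata that add nothing beyond T0. Ward and gender terms would add precision only if those factors are prognostic. The ward difference in usual care makes that plausible for ward, but the documents give no figure.

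The gain does not extend to readmissions, visits or mortality, which have no T0 measurement of the same variable. The case for reporting estimates with intervals applies to all outcomes and does not depend on the correlation.

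**What to change.** Replace the sentence on between-arm tests with wording to this effect:

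- For each scale measured at T0, 3 and 6 months, report the between-arm mean difference with its 95% CI from a linear model with arm, T0 value, ward and gender as main effects. If numbers are too small, use T0 and ward only, by a rule fixed in advance and based on counts alone. Report the residual SD and the correlation of T0 with follow-up.
- For strongly skewed scales, use a transformation or add a rank-based sensitivity analysis.
- For readmissions and death, report counts and risk differences with CIs.
- Describe baseline characteristics by arm without significance tests.

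This needs two or three sentences of analysis wording, trivial programming and no new data. The statistical price is about 1.5% in interval width if T0 turns out not to be prognostic. If the full protocol or analysis plan already specifies such a model, the article's wording need only be aligned with it.
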